**19. Definition of Analysis populations e.g. modified ITT (mITT)**

The **mITT** population is defined as all the schools (excluding schools dropped out after randomization, c.f. Figure 1, whose participation rate was too low along with administration difficulties).

The units of analysis are at both the student's level and school's level for all outcomes.

Schools included in mITT:

1. Completed baseline survey
2. Agreed to continue with study protocol and remain in study post baseline (Delivered 50% of follow-up surveys sessions 2/4)

Child included in mITT:

1. Assented and parent passive or active consent
2. Completed baseline survey
3. Provided reliable substance use (Dep-Ado, all 36 items used to identify SUD) and SURPS (All 23 items) data at baseline and year 5.
4. High Risk status participants (n=709) will be included.

Per-protocol will exclude participants that did not attend the two sessions of intervention.

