**18.c Description of protocol deviation for the trial**

In the end, some schools did require active parental consent for youth to participate in this trial; therefore, not all HR youth were recruited and were provided with interventions in the intervention condition. However, these schools will remain in the study, and considered “compliant”. Only schools that agreed and were able to facilitate follow-up every year were included in the study, regardless of follow-up rate (therefore, compliant). Schools that did not agree to continue to facilitate follow-up of students were considered dropout (non-compliant) and will not be included in **the intent to treat analysis**.

Protocol deviation are defined as departure from the procedures outlined in the protocol. We used a modified intention to treat (mITT) design including only schools that were randomized and followed during 5 years. At the individual level, mITT will be all high-risk students in the schools who consented to a trial and eligible to receive intervention (Regardless of whether or not they received it). Per-protocol analysis at the individual level will exclude the students who did not receive both intervention sessions.

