**18.d Description of which protocol deviation will be summarized**

Protocol deviation (PD) will be classified prior to unblinding of intervention groups.

1. During the recruitment phase, five schools were recruited and drop out after the randomisation. Among those, three schools never launched screening and baseline survey, and so were not included. One school drop out after screening and one school did deliver intervention, but failed to comply with follow-up procedures, so was also dropped from the trial and not included in mITT.
2. There were some deviations related to the data collection and the questionnaire administration. In the DEP-ADO, a missing item (“last 30 days alcohol use”) was not assessed. Therefore, the positive screen was adjusted to “greater or equal to 18” (Red). Truancy is self-reported. The CMS had to be modified to increase ceiling effects (one additional item was added in year 3, 4 and 5). Finally, the academic records were not obtained.
3. Visit completed outside of the planned window since there were two waves of recruitment, students were recruited in the 7th grade in 2012 and 2013.
4. There were also some procedures not performed. We changed intervention adherence criterion. Overall 88% of HR students received intervention, but some schools had poor implementation, so we will control for adherence, rather than require a certain level of implementation). One school closed and half the students could not be followed individually, but school remains in the study, because they provided access to student information so that they could be followed individually. One school missed a follow-up survey in year 4 and instead completed two surveys 7 months apart in the final year: they are considered compliant and in the ITT.

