**26. Analysis methods****26.a Primary analysis methods used for the primary outcome**

The primary analyses will be the estimation of the effect of the intervention on substance use disorders in high-risk youth in intervention conditions relative to their control counterparts, at the year 5 follow-up (48 months post-intervention). The odds ratio (OR) will be used as the measure of intervention effect for the binary substance use disorders outcome. To account for within-cluster (school) variance, intervention effects will be examined using hierarchical generalized linear modelling (HGLM; using the SAS program, Proc GLIMMIX) using a Bernoulli distribution for the binary primary outcome. The HGLM model will be two-levels, with students as the first level, and nested within schools (clusters) as the second level of the model.

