## **27. Missing data**

### **27.a Accounting for Attrition**

Each student will contribute annual observations until his/her end of follow-up (i.e. Grade 11). It is possible that attrition will be non-random or that some students may not show up for some of their annual assessments. To deal with such potential biases due to non-random attrition, individual annual observations will be re-weighted using the Inverse Probability of Weights (IPW), which will be estimated through HGLM model with a binary outcome (being present or absent at a given annual visit) based on the selected students baseline characteristics.

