### **27.a Reporting and assumptions/statistical methods to handle missing data**

As missing primary outcome values (DEP-ADO scores at 48 months post-intervention) might depend on observed data and/or missing data, and due to the large amount of missing data for the binary primary outcome at 48 months post-intervention (see CONSORT flow diagram, Appendix 2), primary analysis will be performed with imputation for missing data using Multiple Imputation (MI). Missing data will be imputed under Missing At Random (MAR) assumption, and odds ratios estimates for each imputed data set will be obtained. The imputation will be repeated 20 times and Rubin's rule will be used to combine estimates and standard errors.

This represents a change to the original analysis protocol, which did not acknowledge that the potential bias in only considering data that from participants who were available for follow-up. Outcomes are expected to be affected by risk status and substance use outcomes, therefore intent-to-treat analysis will include all participants. Furthermore, as missing data is also at random and highly dependent on participant simply being present on the day of testing at school, there are also cases of missing data at only one timepoint of the 5 assessments. Omitting participants on the basis of one missing timepoint (i.e., listwise) would lead to very large attrition and lost data that would otherwise be useful in the evaluation of the outcome (either through estimate final outcome, or by providing outcomes at other timepoints).

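### The child-level mITT rule in SAP section 19 requires year-5 outcome data, so it selects on the primary outcome and conflicts with sections 18.c, 23, 26.c and 27.a; n = 709 is a one-arm count

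*Combined protocol and SAP*

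**What the plan says.** Section 19 of the SAP lists what a child needs to be in the mITT set. The third criterion is that the child "Provided reliable substance use (Dep-Ado, all 36 items used to identify SUD) and SURPS (All 23 items) data at baseline and year 5". The fourth reads "High Risk status participants (n=709) will be included". The primary outcome is DEP-ADO of 18 or more at the fourth follow-up (Appendix 1), which is the year-5, 48-month assessment (section 26.a).

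Other sections describe a different population:

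- Section 18.c: "mITT will be all high-risk students in the schools who consented to a trial and eligible to receive intervention", whether or not they received it. The protocol-deviation section after Appendix 3 repeats this. Neither sets a year-5 condition.
- Section 23: students who stop early are missing at the visits they missed, and their other data stay in the dataset.
- Section 26.c (sensitivity analyses): imputation moves from a sensitivity analysis to the primary and secondary analyses.
- Section 27.a (reporting and methods): there is much missing 48-month outcome data, multiple imputation is primary, and "Outcomes are expected to be affected by risk status and substance use outcomes, therefore intent-to-treat analysis will include all participants".
- Section 27.a (attrition): "individual annual observations will be re-weighted using the Inverse Probability of Weights".

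For schools, section 18.c describes a design "including only schools that were randomized and followed during 5 years", while section 19 asks for two of the four follow-up surveys. Section 18.d records five schools lost after randomisation, of which "one school did deliver intervention, but failed to comply with follow-up procedures, so was also dropped from the trial and not included in mITT".

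**The concern.** Whether the year-5 DEP-ADO is observed is known only after randomisation and can depend on both the intervention and the outcome. A primary set defined by it is no longer the set that randomisation balanced. Appendix 2 says students are lost for academic, conduct or moving reasons, and section 27.a accepts that missingness may depend on unobserved values, so leavers could plausibly have more substance use disorder than stayers. Year-5 SURPS is not part of the outcome at all. SURPS selects high-risk students at the start, so requiring it again at year 5 can only remove more students.

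The conflict also leaves the primary population undefined. Two analysts following the same SAP could include different students and schools, and the choice could be made after the data are seen. The only count given cannot settle it, because it does not describe a two-arm set.

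**Working it through.** **1. The count of 709.** High-risk students in the 15 intervention schools (SAP Table 2): 38 + 56 + 54 + 63 + 56 + 51 + 66 + 52 + 57 + 86 + 14 + 21 + 34 + 36 + 25 = 709. This equals the figure in section 19 exactly. It contains no control student, and it is the denominator for session attendance, so it precedes any year-5 loss. It therefore cannot be the size of a two-arm set restricted to students with year-5 data.

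**2. The student rule against the rest of the plan.** Take a student with complete baseline data who was seen at 12, 24 and 36 months and absent at 48 months.

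| Text | Is this student in the primary set? |
|---|---|
| Section 19, criterion 3 | No |
| Section 18.c and the closing deviation section | Yes |
| Section 23 | Kept in the dataset |
| Sections 26.c and 27.a (imputation) | Yes, outcome imputed |
| Closing Bayesian model | Three visits could contribute, but the population is not restated |

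Under section 19, the number of mITT students with a missing 48-month DEP-ADO is zero at any follow-up rate. The closing section reports that imputation did not converge and replaces it with a multilevel model over years. The analysis dataset named in the printed model code is not described, so the text does not show whether criterion 3 was applied to it.

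**3. The school rule.** One school missed the year-4 survey and ran two surveys seven months apart in the final year. It meets the two-of-four rule in section 19, does not plainly meet the every-year rule in 18.c, and is kept by 18.d. Of the five schools lost after randomisation, three never ran screening or baseline, one left after screening, and one delivered the intervention and then failed on follow-up.

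**4. Illustration of the selection effect.** From SAP section 10: risks of 10% (control) and 5% (intervention), a true odds ratio of (0.05/0.95)/(0.10/0.90) = 0.47. Assumed, because the flow figure is not shown: leavers have 3 times the odds of stayers, and 20% to 30% leave. (Protocol 2.14 gives 80% follow-up at two years in the earlier cluster trial.)

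With overall risk p and leaving fraction f, the stayers' risk s solves (1 − f)s + f × 3s/(1 + 2s) = p.

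- p = 0.10: s = 0.0757 at f = 0.20, and 0.0669 at f = 0.30.
- p = 0.05: s = 0.0368 at f = 0.20, and 0.0324 at f = 0.30.

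| Loss, control / intervention | True OR 1.00 appears as | True OR 0.47 appears as |
|---|---|---|
| 20% / 30% | 0.88 | 0.41 |
| 30% / 20% | 1.14 | 0.53 |
| 25% / 25% | 1.00 | 0.47 |

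For example, (0.0669/0.9331)/(0.0757/0.9243) = 0.88.

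**5. Power.** The plan's figure reproduces with its 2.5% error rate read as one-sided: 1 + (1.960 + 0.842)² × [0.09/50 + 0.0475/50 + 0.35² × (0.10² + 0.05²)]/0.05² = 1 + 7.849 × 0.00428/0.0025 = 14.44, so 15 schools per arm. Power with 15 per arm is 82% at 50 students per school, 76% at 40 (20% lost) and 72% at 35 (30% lost).

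**The case against.** The strongest reply is that criterion 3 is a leftover line. Sections 26.c and 27.a are marked as changes to the analysis plan, section 18.c has no year-5 condition, and 709 is a pre-attrition count, which suggests that nobody was restricting to completers. The closing Bayesian model was chosen so that incomplete data could be used without imputation. Much of this stands. A reader might infer that the primary analysis is a complete-case analysis; the documents do not establish that. They establish a contradiction, with the restrictive version in the section that defines the analysis set and nothing that withdraws it.

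Other tempting inferences also go too far:

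- That the inverse-probability weights have nothing to act on. Weighting observed students is what such weights do, and section 27.a applies them to every annual visit.
- That no imputation is left anywhere. This is true only of the 48-month DEP-ADO. Earlier visits, secondary outcomes and covariates could still be missing.
- That section 21 adds a third conflicting school rule. Its one-follow-up condition concerns enrolment, not analysis.
- That all five lost schools could be restored. Three have no baseline data.
- That the fall in power is the cost of criterion 3. It comes from missing outcomes, and imputation or an all-visits model would recover only part of it.

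**Conclusion.** The point holds as an unresolved contradiction about the primary population, and it should be fixed. Followed as written, section 19 selects the primary set on having the 48-month outcome, leaves imputation of that outcome without a target, and deletes students seen at 12 to 36 months but lost at year 5. The school rules in 18.c and 19 disagree, one school that delivered the intervention is excluded after randomisation, and n = 709 is the intervention-arm total.

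The size of any bias is not known. In the illustration a null effect shows as anything from 0.88 to 1.14 according to which arm loses more, and no bias arises under the null when loss is equal. These figures rest on the assumed threefold odds and assumed loss rates. A reader might infer that the trial's estimate is biased towards benefit; the text supports neither a direction nor an amount. Nor does removing the condition guarantee an unbiased result: that depends on how well observed data explain who leaves.

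**What to change.** - Delete the year-5 requirement from criterion 3 of section 19, for both DEP-ADO and SURPS.
- Define the primary set once: all consenting high-risk students with baseline DEP-ADO and SURPS, analysed in the arm to which their school was randomised, under one stated school rule. Carry the same wording into 18.c, 18.d and the closing deviation section.
- Name one primary method valid under missing at random that includes every such student. The all-visits multilevel model already described would serve, provided the SAP says that its dataset is this population.
- Keep year-5 completers, with inverse-probability weights, as a sensitivity analysis.
- Replace n = 709 by the number of students in each arm.

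A delta-adjusted sensitivity analysis is worth considering but optional. The two lost schools that got as far as screening can enter only if their data are held, which the documents do not say.

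The cost is rewording of the SAP and a small amount of extra analysis.

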**20. Reporting of screening data to describe representativeness of trial sample**

Co-Venture cohort, which includes 76% of all grade 7 students attending 31 secondary schools in the greater Montreal area (Quebec, Canada). This cohort represents 15% of all schools in the area and each of their respective school districts in size and deprivation indexes within 1.5 standard deviation.

Quality control is conducted using both automated algorithm-based functions and manual scanning of data. The DMC provides coded databases to study research assistants and PHD students responsible for data quality control and will oversee all quality control protocols.

We have developed a successful automated system for data quality control which included sham questions ([name] et al., 2010), questions on participant motivation (Seguin, et al., (2009) and testing context (Schumann, et al., 2010) to assess reliability of information. The structure of the questionnaire, the repeat questions/sham questions and the testing context allow for significant confidence interval in the validity of the self-reported data.

Quality control flag applied:

On the primary outcome

- For the DEP-ADO, those who answered positively to the fake drug item (DEPADO Foil) were flagged and 0.4% of DEP-ADO Drug records were rejected.
- Secondly, those who report uncommon substance use (sum of (TRANQ, STEROIDS, SPEED, PCP, LSD, HEROIN, ECSTASY)>2.5) were also flagged and 0.1% of records were rejected.
- The SURPS results should indicate a minimum of variation. In the absence of variation in the answers, results were flagged and 0.4% of records were rejected)

On the secondary outcomes:

- CFT - There seems to be a significant year to year learning effect in this task (0.1% of CFT records rejected)
- The PALP's "worse than chance" QC flag identifies and excludes those with more than 30 commissions or with more than 30 omissions. With that flag, 17.6% of records were rejected.
- Just like the SURPS, if there was no variation in the SDQ answers, answers were rejected and 0.6% of records were rejected).
- For the CMS task, the time duration between the first part and the recall should not be negative, or longer than the time allotted in a period of class

A trial management committee will consist of the study Principal Investigators (PIs) and named collaborators. Monthly meetings will take place between PIs and the trial coordinator and clinician. A full-time trial coordinator will be responsible for ethical aspects of the study, school recruitment, scheduling follow-up assessments and communication. The trial coordinator will be blind to school allocation. The trial coordinator will be expected to publish the trial protocol in Year 2. A full-time clinical post-doctoral researcher will be responsible for all clinical aspects of this trial, including intervention translation, training, teacher supervision, evaluation of treatment integrity, and knowledge transfer and dissemination (training workshops and published therapy manuals). This person will be the only person aware of school allocation to intervention. A full-time research assistant and two PhD students will be employed to assist with data collection, data management, and study write up. They will be blind to treatment allocation. All data entry will be done directly into the web-based assessment platform and separate case report forms (school and participant) will log participant consent, contact information (at school and at home) and whether follow-up was completed.

## 21. Summary of eligibility criteria

Ages Eligible for Study: 12 Years to 17 Years (Child)

Sexes Eligible for Study: All

Accepts Healthy Volunteers: Yes

Selection of Schools:

**Inclusion criteria:** schools (public or private) able to recruit and willing to conduct at least one follow-up survey.

**Exclusion criteria:** Schools cannot be classified as having a majority of their students coded as special needs students, because these schools are smaller and the intervention protocol would have to be tailored for their particular needs.

Selection of high-risk youth:

**Inclusion criteria:** Students are that they be enrolled in Grade 7 and that they have provided active assent and passive parental consent to participate in the longitudinal survey and randomised trial phases of this study. Participants who score 1 standard deviation above the school mean on one of four subscales of the Substance Use Risk Profile Scale (SURPS)  will be selected to participate in the intervention groups, but all students will be followed on outcomes.

**Exclusion criteria:** There are no other exclusion criteria for participants.

## 22. Information to be included in the CONSORT flow diagram

The figure 2 , in Appendix 2, reports the flow of schools and students through the trial in accordance with the Consolidated Standards of Reporting Trials (CONSORT) extension statement for cluster trials . The flow diagram includes the number of eligible and recruited schools, number of eligible and recruited students and then, by allocated group, the number of students who continued through the trial, the number of withdrawing at each time point, the number of lost to follow-up at each time point and the numbers included in the analysis.

## 23. Withdrawal/Follow-up-level of withdrawal

A REB- and school board-approved passive informed consent procedure involves asking parents to contact the school or research team if they do not wish their child to participate in the study. All assenting students will provide active written consent to participate in the study. An additional active parental written consent form will be provided to nine schools who request this procedure in addition to active youth consent.

School students who discontinue completing the data collection prior to the end of trial period were considered as missing data for time points that they missed but their baseline and following present data were kept in the dataset.

### 23.a Level of school withdrawal

Figure 1: Recruitment of schools and dropouts prior to finalization of school sample

[figure not shown]

**23.b Reasons and details of school children withdrawal**

Most students drop out of a trial due to graduating from high school and moving to other schools, but this will not be a problem in this trial, as we do not expect to follow-up students beyond Grade 11. At the student level, the principal reasons of withdrawal are having left school (e.g. moving, conduct problems, academic difficulty). There are few cases of lost students because a school closed and one reported of death in the control condition.

**24. Baseline School and Students characteristics and descriptive statistics**

Baseline characteristics, collected at the time of commencing the trial, will be cross-tabulated according to the randomised group to check for appropriate balance and to provide an overview of the study population, both at the school and individual levels. Visual inspections will be provided to show prevalence/or average of primary/or secondary outcomes within each cluster level (i.e. school level) at each time point over the 5-year trial.

**24.a List of baseline characteristics**

There are summarized in dummy Tables.

**24.b Details on how baseline characteristics will be descriptively summarized**

At the school level, characteristics will include primary and secondary outcomes. At the individual level, variables include demographic variables as well as primary and secondary outcomes. The baseline characteristics of each group will be summarized as the mean, median, standard deviation, quartiles and range (min, max) for continuous variables; frequencies and percentages of individual/schools in each category for categorical variables.

It is expected that individual in the both collected allocated groups will, on average, be similar, given the randomization procedure.

Test of statistical significance will not be systematically done. Only descriptive data, as described above, will be presented. If substantial imbalance between randomization groups is identified in terms of any relevant variables not already being adjusted for in the primary analysis, additional adjusted sensitivity analyses may be performed.

**25. Outcomes****25.a Definition; Description and timing; Specific measurements and units; Any calculation or transformation; Used to derive an outcome**

See variable directory and Tables for description and timing.

